## Abstract

**Background:**

To evaluate the effectiveness of an experimental intervention based on standard diet recommendations plus free Smartphone application (app) and wearable device for weight loss, compared with the standard diet intervention alone, in primary care patients aged 18 years or older who are overweight or obese.

**Methods/design:**

Multicentre randomized, controlled clinical trial. Location: Primary health care centres in the city of Tarragona and surrounding areas. Subjects: 70 primary care patients, aged 18 years or older, with body mass index of 25 g/m2 or greater who wish to lose weight. Description of the intervention: 12 months of standard diet recommendations without (*n* = 35) or with (*n* = 35) assistance of a free Smartphone app that allows the participant to maintain a record of dietary intake and a bracelet monitor that records physical activity. The outcomes will be weight loss at 12 months (primary outcome), changes in physical activity and cardiometabolic risk factors, frequency of app use, and participant satisfaction after 12 months.

**Discussion:**

The results of our study will offer evidence of the effectiveness of an intervention using one of the most popular free apps and wearable devices in achieving weight loss among patients who are overweight or obese. If these new technologies are proven effective in our population, they could be readily incorporated into primary care interventions promoting healthy weight.

The open design and study characteristics make it impossible for the participants and researchers to be blinded to study group assignment. Researchers responsible for data analysis will be blinded to participant allocation.

**Trial registration:**

Clinical Register: NCT02417623. Registered 26 March 2015.

## Background

In Spain, the prevalence of overweight and obesity is increasing. In 1987, 7.4 % of the adult population (aged 18 years and older) had a body mass index (BMI) of 30 kg/m2 or higher (the cut-off for obesity). In 2012, this percentage exceeded 17, and 53.7 % of the adult population met the definition of obesity or overweight [1]. The adoption of diets high in fat and refined sugars, accompanied by a marked increase in sedentary behaviours are the primary risk factors for the explosive rise in overweigh or obesity [2]. Recently, have appeared new products such as Smartphone applications and wearable device that may improve these modifiable risk factors for obesity.

Obesity is clearly associated with increased morbidity and mortality [3, 4]. As BMI increases, a gradual but continual increase in relative risk of mortality has been reported, with the greatest increase observed when BMI exceeds 30 kg/m2 [5]. There is strong evidence that weight loss in overweigh and obese individuals reduce risk factors for diabetes and cardiovascular disease [6].

Treatments for overweight and obesity obtain disparate results. In one review of 14 studies of weight-loss interventions in young adults (18–25 years old), the authors conclude that combined interventions seem to have a beneficial effect on weight loss (−2.96 kg, 95%CI −4.4 to −1.5 kg). The most significant weight reduction was obtained by combining diet, exercise and motivational strategies [7,8]. Considering the ubiquity of Smartphone use, mobile applications (apps) that combine multiple strategies offer an attractive “modern” alternative to traditional weight-loss programs.

According to the 15th edition of “The Information Society in Spain”, published in 2015 by the foundation of Spain’s national phone company, mobile phones are owned by almost 95.5 % of the world population, and by almost 120 % of the European population. More than 80 % of mobile phone users have Smartphone and more tablets than laptop computers are sold as intelligent terminals. The nascent field of mobile health (mHealth) is rapidly expanding; experts estimate that as many as 100,000 health-related apps were available in the first trimester of 2014 [9] . Many of these apps aim to help persons change behaviours to achieve weight loss by increasing physical activity or recording dietary intake. According to data from Price Waterhouse Cooper and GSMA, by 2017 the use of mHealth could save the health care budgets of European countries up to 100,000 million euros [10]. Interventions in the primary care setting have the added benefit of ongoing professional support and monitoring, which could contribute to better patient outcomes.

The hypothesis that some overweight and obese subjects do not lose weight while following a low-caloric diet because their energy intake is substantially higher than reported is based on the finding that whereas many people underreporting is greater in overweight and obese people [11]. Overweight and obese subjects may also overestimate the energy that may therefore require less energy intake to maintain body weight than their exercise history suggests. A study found that the discrepancy between self-reported and actual calorie intake and physical activity, estimated as being as large as 47+/−16 % and 51+/−75 %, respectively [12]. Another study found that consistent self-monitoring of exercise was associated with fewer difficulties with exercise and greater exercise and weight loss [13]. This suggests that providing patients with tools that will help to record dietary intake or physical activity more accurately could increase the effectiveness of interventions designed to prevent overweight/obesity [11,14]. A study found that users of a mobile app which self-monitoring physical activity and dietary intake consumed less energy than those self-monitoring using a paper journal [15]. An a recent systematic review found behavioural changes increased to diet monitoring (*p* < 0.001) [16].

Unfortunately, many of Smartphone apps are not very sophisticated and deliver a limited or dubious benefit. Therefore, the need to regulate this growing market is becoming a concern, with researchers emphasizing the need for studies that will contribute scientific evidence about the true impact of this type of apps . A limited number of intervention studies have been designed to assess the effectiveness of Smartphone applications for weight loss [15, 17–22] and for increase physical activity [15, 20, 23]. All of these studies had small sample sizes, none of them incorporated a wearable device, and none of them were done in a setting resembling the primary care system in Spain.

In recent months, wearable devices have taken the electronic devices market by storm. They offer processing capacity and Internet connectivity, and of particular interest to this project are the wearable knows as SmartBands that can monitor physical activity. In the first quarter of 2014, 2.7 million SmartBands were sold [9]. The SmartBands have adopted gamification as a means to increase initiation and retention of desired behaviours. Gamification is the use of game design elements in nongame contexts, include the use of game-like rewards and incentives and sustain habits of individuals over time. A comprehensive review of gamification use in health and fitness found a lack of integrating important elements of behavioural theory form the app industry, which can potentially impact the efficacy of gamification apps to change behaviour [24]. Although the use of this tactic in health and fitness mobile apps has increased, little to no in-depth inquire into its effectiveness and appropriate functionality [24].

### Objectives

The objective of the present study is to evaluate the effectiveness of a weight loss intervention based on standard diet recommendations plus a free Smartphone application (app) and wearable device, compared to the standard evidence-based diet intervention alone (control), in primary care patients aged 18 years or older who are overweight or obese.

## Methods

### Study design

Randomized, controlled trial with one experimental group and a control group (Participant Flowchart, Fig. 1).

**Fig. 1 Fig1:**
[figure not shown]
Participant Flowchart

### Blinding

The type of intervention makes it impossible to blind participants and health professionals to participants’ study group assignment. However, those responsible for data analysis will be blinded to group status.

#### Participants and settings

Participants (*n* = 70) will be recruited from two primary healthcare centres in the city of Tarragona and surrounding areas and randomly assigned to a standard diet intervention (**control group**, n = 35) or standard diet intervention plus a free Smartphone application and wearable device (**experimental group**, *n* = 35). A personalized letter will be sent to the attention of the centre administrators, requesting collaboration and providing a copy of the study protocol. Within 2 weeks, the administrators will be contacted by telephone to confirm their participation.

##### Patient inclusion criteria:

a) Adults aged 18 years or older with BMI ≥25 kg/m2; b) Medical history available in the participating primary care centre; c) Access to a mobile device with Android operating system or iOS; and d) Consent to participate.

##### Patient exclusion criteria:

a) Morbid obesity, defined as BMI >40; b) Secondary obesity (e.g., a disease of the endocrine system); c) Eating disorder diagnosed in any family member (not only the patient); d) Any major comorbidity requiring specific treatment (e.g., type 1 diabetes mellitus, severe mental disease); i) Women who are pregnant or want to be pregnant within 12 months; f) Participation in a weight-loss program or taking a weight-loss medication at the time of recruitment; h): Use of an operating system other than Android or iOS; and i) No consent to participate.

### Sample size

Accepting an alpha risk of 0.05 and a beta risk of 0.2 in a two-sided test, **70** subjects are necessary in each group, with an estimated 30 % loss to follow-up, to recognize as statistically significant a difference greater than or equal to 3.9 kg [22]. The common standard deviation is assumed to be 4.826 kg.

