### Screening and randomization

During the recruitment period, and until the calculated sample size has been achieved, participating primary care doctors and nurses who see patients aged 18 and older, for any reason, meeting the study definition of overweight or obesity will invite the patient to participate in the study (Fig. 1: Participant Flowchart). If the patient does not meet any exclusion criteria and agrees to participate, the health professional will schedule a primary care visit with a doctor or nurse participating in the study (**Visit 0**, screening) within about a week.

During the screening visit, eligible participants will be assigned a participation code. The randomization unit will be the individual patient, assigned 1:1 to the experimental or control groups. An independent investigator will be responsible for generating the allocation sequence using non-commercial Epidat 3.0 software. During this same visit, all participants will begin the standard diet intervention. In addition, **experimental group participants** will download the free app, receive a bracelet monitor (wearable device), and learn to use them (along with take-home instructions).

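### The sample-size statement asks for 70 subjects per group, but its own inputs give about 35 per group, which is the 70 in total that the trial plans to enrol

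*Protocol article*

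**What the plan says.** The Sample size section sets its error rates with "Accepting an alpha risk of 0.05 and a beta risk of 0.2 in a two-sided test". It assumes 30% loss to follow-up and a common standard deviation of 4.826 kg, and aims to detect "a difference greater than or equal to 3.9 kg". From this it concludes that "70 subjects are necessary in each group", which makes 140 in total.

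Two other places give a different size. The Abstract (Methods/design) has "Subjects: 70 primary care patients, aged 18 years or older", split 35 and 35. Participants and settings has "Participants (*n* = 70) will be recruited from two primary healthcare centres", again with 35 control and 35 experimental participants.

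Screening and randomization fixes 1:1 allocation and continues recruitment "until the calculated sample size has been achieved", without repeating a number.

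**The concern.** The required size in the Sample size section is twice the enrolment planned everywhere else. A reader who trusts that section would conclude that the trial is designed to enrol half the subjects it needs and is badly underpowered. A reader who trusts the Abstract would see no problem.

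The recruitment rule adds a practical side. It points to the calculated sample size, and the only section that presents a calculation is the one that says 70 per group. Taken literally, recruitment ends at 140; by the Abstract and Participants and settings, it ends at 70. Finishing as planned at 70 could then look like a failure to reach target.

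**Working it through.** **Inputs** (Sample size section, except the last):
- two-sided alpha 0.05, so z = 1.960
- beta 0.2, so z = 0.842
- difference d = 3.9 kg
- common SD s = 4.826 kg
- loss to follow-up 30%
- allocation 1:1 (Screening and randomization)

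**Step 1: evaluable subjects per group, normal approximation.**
n = 2 × (1.960 + 0.842)² × (s/d)²
= 2 × 7.85 × (4.826/3.9)²
= 2 × 7.85 × 1.531
= 24.04

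**Step 2: allow for loss.**
24.04 / (1 − 0.30) = 34.3, so 35 per group and 70 in total. This is the enrolment in the Abstract and in Participants and settings. The figure of 70 is reproduced as a total, not as a group size.

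**Step 3: does another reasonable calculation give 70 per group?**

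| Variant | Evaluable per group | Enrolled per group |
|---|---|---|
| Normal, rounded up before inflating | 25 | 36 |
| Normal, multiplied by 1.3 instead of divided by 0.7 | 25 | 33 |
| Exact t, unrounded | 25.03 | 35.8, so 36 |
| Exact t, rounded up before inflating | 26 | 38 |
| One-sided test | 19 | 28 |
| Power 0.90 | 33 | 48 |
| Power 0.95 | 40 | 58 |
| Bonferroni over three time points | 33 | 48 |

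The first four rows use the stated error rates and stay between 33 and 38. The last four depart from the stated plan and still fall short of 70.

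**Step 4: what each size would deliver for 3.9 kg.**
- 35 per group: 35 × 0.70 = 24.5 evaluable. Power is 79% by t-test and about 81% by the normal approximation.
- 70 per group: 70 × 0.70 = 49 evaluable. Power is 97.7% by t-test and 97.9% by the normal approximation. At 80% power, the detectable difference would be about 2.73 kg (normal) or 2.76 kg (t-test), not 3.9 kg.

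Only 35 per group agrees with the stated beta of 0.2 and the stated 3.9 kg.

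**The case against.** The strongest reply concerns consequence rather than arithmetic. Two sections agree on 70 in total and give both group sizes, the inputs support that number, and one sentence is out of line. Enrolment to 140 is unlikely in practice. A careful reader can also recover the true power, because every input is printed. This is fair: the design itself is coherent, and the error lies in how one figure is labelled.

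A second reply is that 35 is not exact. It follows if the unrounded 24.04 is inflated; rounding first or using the t distribution gives 36 to 38. At 24 to 25 evaluable per group, t-test power is 78% to 80%, at or just below the stated level. This also stands, and it is why the corrected sentence should say about 80%. It does not touch a discrepancy of a factor of two.

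A third reply is that one route does reach 70 per group. If the variance is doubled (SD 4.826 × √2 = 6.825 kg), n = 2 × 24.04 = 48.07, rounded up to 49, and 49/0.70 = 70. But the section calls 4.826 kg the common standard deviation, and the formula for two means already includes the factor of two. This route would also leave the planned 35 per group at half the required size: with 24.5 evaluable, 3.9 / (6.825 × √(2/24.5)) = 2.00, and power is Φ(2.00 − 1.96), about 52%. The conflict between sections would remain. The route is a reason to have the authors confirm the calculation, not a defence of the text.

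**Conclusion.** The concern holds. The stated requirement of 70 per group is wrong on the section's own inputs, by a factor of two, and contradicts the enrolment given in two other places. The inputs give 35 per group by the normal approximation with unrounded inflation, and up to 38 with other rounding or the exact t-test.

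The most plausible explanation is that the total of 70 was written as a group size. On that reading the planned enrolment of 35 + 35 is adequate, with about 80% power for 3.9 kg. This rests on the printed inputs, a two-sample comparison of means, and 4.826 kg being the SD within each group. The error needs correction because it misstates the basis for the trial's size and because the recruitment rule depends on that size.

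**What to change.** Replace the statement in the Sample size section with one to this effect: 35 subjects in each group (70 in total), allowing for 30% loss to follow-up, give about 80% power to detect a difference of 3.9 kg with a common SD of 4.826 kg, two-sided alpha 0.05. In Screening and randomization, name 70 in total as the number at which recruitment ends.

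Before doing so, the authors should check their original calculation to confirm that 70 was its total. If a different SD was intended, they should state it and correct the group sizes in the Abstract and in Participants and settings instead.

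If 70 was the total, the cost is one reworded sentence and one added number, with no change to enrolment.

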### Screening and randomization

During the recruitment period, and until the calculated sample size has been achieved, participating primary care doctors and nurses who see patients aged 18 and older, for any reason, meeting the study definition of overweight or obesity will invite the patient to participate in the study (Fig. 1: Participant Flowchart). If the patient does not meet any exclusion criteria and agrees to participate, the health professional will schedule a primary care visit with a doctor or nurse participating in the study (**Visit 0**, screening) within about a week.

During the screening visit, eligible participants will be assigned a participation code. The randomization unit will be the individual patient, assigned 1:1 to the experimental or control groups. An independent investigator will be responsible for generating the allocation sequence using non-commercial Epidat 3.0 software. During this same visit, all participants will begin the standard diet intervention. In addition, **experimental group participants** will download the free app, receive a bracelet monitor (wearable device), and learn to use them (along with take-home instructions).

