### Data collection

#### Demographics and medical history

During **visit 1 (baseline)** and **visit 14 (end of follow-up)**, an interviewer-guided survey will be completed by the patient and primary care nurse or doctor and blood tests will be ordered. The following data will be obtained: (a) Sociodemographics– sex, birthdate, educational level, profession and social rank, categorized using the National Classification of Occupations (*Clasificación Nacional de Ocupaciones* [CNO-2011]); (b) History of diseases and use of toxic substances – tobacco and number of cigarettes smoked per day, amount (gr) of alcohol consumed per week, other toxic substances, and usual medication; and (c) Blood test: complete blood count, renal function, liver function, lipid profile, glycaemia.

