#### Dietary history and physical activity

At baseline (visit 1) and at end of follow-up (visit 14) the nurse will register food intake using two methods, a validated food frequency questionnaire [26] and 24-h recall, to arrive at an average daily energy consumption estimate (in calories) and determine an individualized dietary pattern. At baseline (visit 1), and at visits 3, 6, and 12 months (end of follow-up), physical activity will be measured with two brief validated questionnaires [27], administered in the participant’s preferred language (Catalan or Spanish).

Moreover, all participants will encouraged to self-record their food intake, using the Smartphone in the experimental group and a traditional paper-based food diary in the control group. These records will be reviewed by a nurse at baseline, at 6 and 12 months.

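### The only stated baseline for diet, physical activity and blood tests (Visit 1) comes after allocation and start of treatment (Visit 0), and no reference visit is named for weight change

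*Protocol article*

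**What the plan says.** Under Screening and randomization, the protocol article puts four steps in the screening visit, Visit 0:

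- Coding: "During the screening visit, eligible participants will be assigned a participation code".
- Allocation: "The randomization unit will be the individual patient, assigned 1:1 to the experimental or control groups".
- Start of the diet in both arms: "During this same visit, all participants will begin the standard diet intervention".
- Start of the technology in the experimental arm, whose participants "will download the free app, receive a bracelet monitor (wearable device), and learn to use them".

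The data-collection sections attach the word baseline to the next visit:

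- Survey and blood tests (Demographics and medical history): "During visit 1 (baseline) and visit 14 (end of follow-up), an interviewer-guided survey will be completed". The blood tests are ordered at these visits.
- Food intake (Dietary history and physical activity): "At baseline (visit 1) and at end of follow-up (visit 14) the nurse will register food intake using two methods".
- Physical activity (same section): "At baseline (visit 1), and at visits 3, 6, and 12 months (end of follow-up), physical activity will be measured".

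The Physical examination section has weight, waist and blood pressure taken at every study visit and does not say whether Visit 0 counts. The Outcomes section defines the primary outcome as change in body weight at 3, 6 and 12 months and names no visit from which change is counted.

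**The concern.** A baseline should precede allocation, so that the arms differ on it only by chance. Here the participant has been allocated and has started the diet before the visit that is called baseline. In the experimental arm the app and bracelet are in use as well. According to the Experimental group section, these tools set a calorie target and daily step or distance challenges, so they act on the behaviours that the Visit 1 questionnaires measure.

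Three things are at stake:

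- A between-arm effect already present at Visit 1 is removed from the estimated change.
- In an open trial, self-report instruments called baseline are answered by people who know their arm.
- The comparability analysis planned under Statistical analysis would mix chance imbalance with early treatment effect for every characteristic that treatment can move.

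A value from before treatment that was never collected cannot be recovered at analysis.

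**Working it through.** **1. Order of events, by outcome**

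| Measure | Stated baseline | Could a value from before allocation exist? |
|---|---|---|
| Physical activity | Visit 1 | None stated |
| Dietary pattern (food-frequency questionnaire, 24-h recall) | Visit 1 | None stated |
| Glucose, lipids, GPT | Visit 1 (ordered then) | None stated |
| Weight, BMI, waist, blood pressure | Reference visit not named | Possibly, if Visit 0 counts as a study visit and the measurement precedes allocation |

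Allocation, diet, app and bracelet are all placed at Visit 0. Nothing in the article calls Visit 0 the baseline or says that the Visit 1 measurements come before allocation.

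**2. Is this only a slip in numbering?**

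Two details suggest that it is not. The diet section gives 15 visits in total, and numbering from 0 to 14 gives 14 − 0 + 1 = 15, so Visit 0 appears to count as an intervention visit. Also, self-kept food records, which the experimental arm keeps on the smartphone, are to be reviewed by a nurse at baseline. That makes sense only if recording began earlier.

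**3. How long is the gap?**

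It is not stated. The two-weekly schedule suggests about two weeks, but the schedule does not add up well enough to date the visits. Contacts every two weeks from week 0 to week 12 number 7, and monthly contacts for months 4 to 12 number 9. That is 7 + 9 = 16, not 15.

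**4. Effect on the estimate**

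Let D1 be the between-arm difference already caused by the app and bracelet at Visit 1, and D12 the difference at 12 months. The change from Visit 1 then estimates D12 − D1.

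- If D1 = 0, there is no bias.
- If D1 has the same sign as D12 and is smaller, the effect is understated by the fraction D1/D12.
- If an early response fades so that D1 exceeds D12, the sign reverses.

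Both arms start the diet at Visit 0, so a diet response common to both cancels in the between-arm comparison, although within-arm change is understated.

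The article gives no value for D1 for any outcome, so the bias cannot be computed.

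**5. Illustration for weight, only if Visit 1 weight were the reference**

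The inputs, from the Sample size section, are a difference of 3.9 kg, SD 4.826 kg, two-sided alpha 0.05 and 30 % loss. With 35 per arm, 35 × 0.70 = 24.5 are evaluable. By the normal approximation, power = Φ(d / (4.826 × √(2/24.5)) − 1.96), where the standard error is 1.379 kg.

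| Assumed share of effect lost | d (kg) | Power |
|---|---|---|
| 0 % | 3.90 | 80.7 % |
| 5 % | 3.70 | 76.6 % |
| 10 % | 3.51 | 72.1 % |
| 20 % | 3.12 | 61.9 % |

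The shares are assumptions without support in the article. The table shows sensitivity and is not an estimate of the loss.

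**The case against.** A reader might infer that every change from baseline, including the primary weight outcome, starts after treatment, and that power for weight falls accordingly. The article does not support this. Neither section that labels Visit 1 as baseline covers weight. Anthropometrics are recorded at every visit, and eligibility depends on BMI, so a weight is needed by Visit 0. For weight the reference is undefined, which is not the same as being stated to be post-treatment. The illustration above applies only if Visit 1 weight is chosen.

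Two further inferences go too far:

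- **Adjusting away the effect.** The planned analysis is a two-level repeated-measures model, and the article does not name a baseline value as a covariate. Covariates enter if p < 0.30 in bivariate analysis, so a Visit 1 value moved by treatment could enter, but this is not certain.
- **Breach of intention to treat.** A repeated-measures model does not in itself require a Visit 1 value. A participant who never returns after Visit 0 lacks follow-up whichever visit is called baseline.

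It is also fair to say that the participant flowchart is not shown and might clarify the order, that the interval between the visits could be short, and that fixed characteristics such as sex, birth date and education are unaffected.

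These objections narrow the point. They leave standing that, for physical activity, diet and blood tests, the text gives one baseline and places it after the start of treatment.

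**Conclusion.** The concern holds for physical activity, dietary pattern, glucose, lipids and GPT: followed as written, their only stated baseline is post-randomisation, post-treatment and taken with allocation known. For weight, BMI, waist and blood pressure the finding is weaker. A Visit 0 value may exist, but no reference visit is named, and the only visit labelled baseline is Visit 1.

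The direction of bias is towards no effect if the early effect has the same sign as the later one and is smaller. Its size cannot be derived from the article. The conclusion rests on reading the visit numbers literally and on the absence of any text that reconciles them. Bias in the primary outcome is possible but not shown.

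**What to change.** Reconcile Screening and randomization, Demographics and medical history, Physical examination, Dietary history and physical activity, and Outcomes, so that all baseline questionnaires, anthropometrics and the blood draw are complete before allocation is revealed and before the diet, app or bracelet starts. Either of two routes achieves this:

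- Do everything at Visit 0, ahead of allocation.
- Move allocation and the start of all interventions, the diet included, to after the Visit 1 measurements. Moving only allocation and the app and bracelet would leave the baseline after the start of the diet in both arms.

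In Outcomes, name the pre-allocation weight as the reference for change in weight, BMI and waist, and state the reference for blood pressure too. The blood sample must be drawn, not only ordered, before the start.

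The cost is a longer first visit or a short delay in starting the intervention. No additional participants are needed. Whether the blood draw needs a separate appointment depends on local arrangements that the article does not describe.
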